### Intervention

#### Usual care

The patient is usually followed-up by the hospital oncologist or haematologist every month for the first 3 months after OAA initiation and then, if well tolerated, at 3-month intervals. The aim is to ensure the clinical and biological response to the treatment and to monitor tolerance. Changes in prescriptions can occur if needed (eg, decrease in OAA dosage). There is no intervention from the hospital pharmacist, as OAA is provided by the community pharmacist every month. When dispensing the drug, the community pharmacist may give some advice on how to take it, particularly in relation to other treatments taken by the patient.

#### The ONCORAL programme

The ONCORAL multidisciplinary programme has been described elsewhere.^20 21^ Monthly interviews are carried out with a hospital pharmacist and/or a nurse after each consultation with the oncologist or haematologist in the hospital or by telephone if no consultation is scheduled. It is carried out for the entire duration of the OAA treatment and will be assessed in the context of the study up to 12 months after beginning of treatment (ie, patient’s inclusion).

Briefly, the therapeutic education sessions are personalised, taking into account the specific needs of each patient. They cover issues relating to understanding the medication plan, including all drugs prescribed to the patient, and the management of side effects and the prevention of drug–drug interaction, including self-medication. If the pharmacist detects an interaction, the prescribing physician is contacted to manage it jointly.

All the community health professionals involved in the patient’s care (ie, the attending general practitioner, the community pharmacist, and the home nurse, if any) are informed of the patient’s participation in the ONCORAL programme and of all relevant information gathered during the sessions, and are encouraged to share all advice given to the patient using an individual liaison booklet.

### Outcome measures and data collection

The main objective of this medico-economic study is to assess the cost-effectiveness, in terms of cost per quality adjusted life years (QALY), of the ONCORAL programme for the drug management monitoring of outpatients treated with OAA and at risk of developing drug-related iatrogenic events compared with usual care.

#### Primary outcome

The primary outcome will be the estimation of the incremental cost-effectiveness ratio (ICER) at 12 months between the ONCORAL programme and usual care.

The impact of OAA management monitoring will be measured using QALYs that takes into account both survival and quality of life, which is particularly relevant in cancer. The number of QALYs will be assessed using survival time and the 3-level version of the EuroQol 5 Dimensions questionnaire (EQ-5D-3L).^22^

Cost calculations will include hospital-related and ambulatory costs over the 12-month period of the study, from a French health insurance perspective and a hospital perspective.

#### Secondary outcomes

Evaluation of OAA management consequences:Relative-dose intensity (RDI), defined as the ratio of the prescribed dose of the OAA to the dose recommended in the Summary of Product Characteristics approved as part of the marketing authorisation, with a description of the types and reasons for change in dosage.Adherence to OAA treatment, measured using a 6-item scale combined with the prescription refill rate.Number and type of adverse drug events related to OAA and their grade (2, 3, or 4) according to the Common Terminology Criteria for Adverse events (CTCAE V.5.0) developed by the US National Cancer Institute.Number and type of drug–drug interactions related to OAA.Number and type of proven medication errors, with description of their clinical consequences, according to the National Coordinating Council for Medication Error Reporting and Prevention (NCC MERP).Evaluation of clinical outcomes:Overall survival and progression-free survival.Cancer-related quality of life, measured using the EORTC QLQ-C30 questionnaire.Description of patient-reported outcomes (PROs) in relation to their treatment:Patient satisfaction with OAA treatment, measured by the Treatment Satisfaction with Medicines Questionnaire (SATMED-Q).^23^
Patient cognitive and emotional representations of illness, measured by the Brief Illness Perception Questionnaire (Brief IPQ).^24^
Patient cognitive representations of medication, measured by the Beliefs about Medicines Questionnaire (BMQ).^25^
Social support perceived by the patient.^26^
Patient health locus of control according to the Therapeutic Self-Care measure.^27^
Budget impact analysis estimating the annual financial impact of the adoption of the ONCORAL programme on the budget of the French national health insurance system.Description of patient and health professional satisfaction with the ONCORAL programme, measured using a visual analogue scale.

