## Methods and analysis

### Study design and settings

A prospective controlled study with individual open-label randomisation was designed to compare two groups of outpatients treated with OAA at risk of developing a drug-related iatrogenic event and benefiting from follow-up consultations by an oncologist or haematologist from the Lyon Sud Hospital of the *Hospices Civils de Lyon*, France. Patients randomised to the intervention group will benefit from the ONCORAL programme, with enhanced multidisciplinary management involving hospital and community health professionals while patients randomised to the control group will be managed according to usual care.

Each eligible participant will be recruited following the consultation for an initiation or change of OAA with a hospital oncologist or haematologist. If the patient is ambulatory, deemed to be at important risk of developing drug-related iatrogenic events with OAA, and meets all the inclusion criteria (table 1), he will be informed orally and with a detailed written notice by the investigator. Randomisation will be set up after obtaining informed consent, in accordance with the principals of good clinical practice.

**Table 1 T1:** Patient eligibility criteria

Inclusion criteria	Exclusion criteria
Adult over 18 years of age	Treatment with OAA under a clinical trial or compassionate use
Diagnosed cancer	Treatment managed at home by a caregiver exclusively
Ambulatory status (not hospitalised for the management and treatment of the cancer)	No declared attending physician
Initiation or change of OAA (indication in the context of the marketing authorisation)	No or ≥2 declared regular community pharmacies
Sufficient autonomy to manage the treatment at home*	Participation in a clinical trial that may modify the costs of care
No major psychiatric cognitive disorder likely to interfere with the ONCORAL programme*	Legal protection or institutionalisation
Considered by the oncologist to be at risk of drug-related adverse events, or to have three or more of the following risk factors for developing a drug-related adverse event:	
≥2 OAA prescribed in combination	
≥2 lines of treatment	
Combination with an injectable chemotherapy protocol	
Discontinuous OAA regimen	
≥2 associated chronic conditions	
≥5 associated drugs including OAA	
Creatinine clearance<60 mL/min	
Frailties and psychosocial conditions (isolated patient, foreigner, and limited autonomy)	

*According to the treating oncologist.

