OAA, oral anticancer agent.

The allocation of patients to the two study groups will be done via a centralised online randomisation system, in an unbalanced ratio 2:1 between the ONCORAL programme and usual care. Allocation will not be blinded to participants, medical staff, nor the clinical trial staff.

During the course of the study, in the event of a change in treatment and/or complete discontinuation of OAA, the patient will be withdrawn from the study; however, its data will be considered and analysed.

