### Statistical considerations

#### Sample size calculation

The sample size was based on RDI, as it is associated with the effectiveness of OAA. According to the information available in the literature at the time of the study design, its value was 0.70 in usual care.^28^ We assume that the ONCORAL programme will achieve the RDI of 0.85. For an unbalanced 2:1 ratio in favour of the ONCORAL programme, a sample of 130 patients in the ONCORAL group and 65 in the usual care group will achieve a power of 80% at a 0.05 two-sided significance to detect a difference of 0.15 with a SD of 0.35. To take into account early withdrawal from the study, a total of 215 patients will be included in the study (143 in the ONCORAL group and 72 in the usual care group).

The number of patients treated with OAA in the study centre is approximately 350 per year, which will allow the recruitment of the expected number of subjects.

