#### Main analyses

The ICER will be expressed as the extra cost in euros per QALY gained following the introduction of the ONCORAL programme compared with the control group:^29^

$$ICER=\frac{C_{Oncoral}-C_{Control}}{QALY_{Oncoral}-QALY_{Control}}$$

where 
$C_{Oncoral}$
 and 
$C_{Control}$
 are the mean cost per patient in each group, and 
${QALY}_{Oncoral}$
 and 
${QALY}_{Control}$
 the mean number of QALY in each group.

The principle of calculating QALYs is to weight the time spent in health states by the preference scores associated with these states. Multiattribute health state classification systems are one of the methods of valuing health states. The EQ-5D-3L self-administered questionnaire is a multiattribute health state classification system whose preference scores are validated in France.^30^ Once the health states are described by the EQ-5D-3L, each of them is individually associated with the corresponding preference score.

A univariate sensitivity analysis will be performed to test the robustness of the cost-effectiveness analysis results and to identify the most sensitive parameters, using a Tornado diagram. The bootstrap method will be used to analyse the sampling uncertainty: 95% CIs of the parameters will be computed; and the joint uncertainty of costs and QALYs will be analysed using cost-effectiveness acceptability curves, which will represent the probability that the ONCORAL programme will be cost-effective at different willingness-to-pay thresholds.

Concerning the primary outcome, a complete case analysis, based on patients for whom all cost and effectiveness data are available, will be performed; an intention-to-treat analysis will be performed in the whole population after imputation of missing data.

Data regarding secondary outcomes will be described for each group. Missing data will be documented but there will be no imputation for secondary outcomes. A Kaplan-Meier model will be used to estimate the overall and the progression-free survival rates up to 12 months in each group, and a log-rank test will be implemented to compare them. Mixed models for repeated measures will be used to estimate the evolution of the different PROs and of cancer-related quality of life.

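### Relative-dose intensity, the outcome that sizes the trial, includes a dose set before randomisation but is only described by arm; adjusting for the starting-dose ratio would gain precision at no cost

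*Protocol article*

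**What the plan says.** Five statements in the protocol article bear on this point.

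- **Definition (Secondary outcomes).** RDI is "defined as the ratio of the prescribed dose of the OAA to the dose recommended in the Summary of Product Characteristics", accompanied by "with a description of the types and reasons for change in dosage". The ratio is a level; nothing in the definition refers to the dose at inclusion.
- **Timing (Study design and settings).** "Each eligible participant will be recruited following the consultation for an initiation or change of OAA", and "Randomisation will be set up after obtaining informed consent". Prescribing therefore comes first, then consent, then allocation.
- **Sizing (Sample size calculation).** RDI is expected to be 0.70 under usual care and 0.85 with the programme. With 130 and 65 patients, the trial is to have 80% power at two-sided 0.05 "to detect a difference of 0.15 with a SD of 0.35".
- **Analysis (Main analyses).** "Data regarding secondary outcomes will be described for each group". Log-rank tests are then named for survival, and mixed models for patient-reported outcomes and cancer-related quality of life. No model is named for RDI.
- **Purpose (Discussion).** RDI is presented there as capturing the prescription changes that follow treatment toxicity.

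A statistical analysis plan is announced at the end of Statistical considerations. It was not available for this review.

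**The concern.** A patient whose first prescription is below the label dose starts with a low ratio, whichever arm is then allocated. The programme can act only on what follows, since its sessions come after the medical consultation ("Monthly interviews are carried out with a hospital pharmacist and/or a nurse after each consultation with the oncologist or haematologist").

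The risk factors in Table 1 include reduced creatinine clearance, frailty, five or more drugs, and combination regimens. They make varied starting doses plausible, although the article gives no distribution.

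Two things are at stake.

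- **Precision.** Spread in starting doses is part of the spread in RDI. If it is left in, the interval for the arm difference is wider than it need be, on the only outcome with a stated power.
- **Interpretation.** The Discussion wants RDI to show changes in prescription, but the defined ratio also counts where each patient began. A reduced starting dose that never changes gives a low RDI with no toxicity-driven change behind it.

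**Working it through.** **Inputs from Sample size calculation:** difference 0.15, SD 0.35, two-sided alpha 0.05, power 80%, 130 v 65 patients.

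**Input not in the article:** the within-arm correlation r between the starting-dose ratio and RDI. It is assumed, and a range is shown. The article also does not give the period over which RDI is computed; I assume that the first prescription counts in it.

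**Step 1. Reproduce the plan's figure.**
Controls needed = (1 + 1/2) × SD² × (1.960 + 0.842)² / difference² = 1.5 × 0.1225 × 7.85 / 0.0225 = 64.1, rounded up to 65. With 2:1 allocation this gives 130 in the programme arm. The stated 130 + 65 reproduces.

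**Step 2. Unadjusted precision.**
- SE = 0.35 × √(1/130 + 1/65) = 0.35 × 0.1519 = 0.0532.
- Power = Φ(0.15/0.0532 − 1.960) = Φ(0.86) = 80.5% (80.2% by noncentral t).
- 95% CI half-width = 1.972 × 0.0532 = 0.105.

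**Step 3. Adjusted precision.**
Residual SD = 0.35 × √(1 − r²), put through the same formulas at 130 v 65:

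| Assumed r | Residual SD | Power | CI half-width | Total N for 80% power |
|---|---|---|---|---|
| 0 | 0.350 | 80.5% | 0.105 | 195 |
| 0.2 | 0.343 | 82.1% | 0.103 | 186 |
| 0.3 | 0.334 | 84.1% | 0.100 | 177 |
| 0.5 | 0.303 | 90.3% | 0.091 | 147 |
| 0.7 | 0.250 | 97.7% | 0.075 | 99 |

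The last column only expresses the gain in patients. It is not a case for recruiting fewer.

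**Step 4. Chance imbalance in starting dose.**
If the starting ratio has an assumed SD of 0.10, 0.15 or 0.20, its difference between arms has SE = SD × 0.1519 = 0.015, 0.023 or 0.030. The 95% ranges are ±0.030, ±0.045 and ±0.060, that is 20%, 30% and 40% of the 0.15 target. These are differences in starting ratio; they pass to RDI in full only if the starting ratio carries through one for one. If 0.35 is the SD of RDI as defined, this variation is already inside the 0.0532 of step 2 and must not be added to it.

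**The case against.** The strongest objection is that covariates for a secondary outcome belong in the statistical analysis plan, which is announced but not shown, and that stating a description by group is not a decision against adjustment. This stands in part: the absence of a covariate from the article is not an error. The suggestion remains useful because the article names methods for other secondary outcomes but, for the outcome that sets the sample size, states only a description. A better method is available using a value that computing RDI already requires.

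A reader might infer three stronger claims. The article does not support them.

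- **That the raw comparison is biased.** Allocation is randomised ("The allocation of patients to the two study groups will be done via a centralised online randomisation system"), so starting doses are balanced in expectation, and the standard error covers chance imbalance.
- **That the sample size is wrong.** It reproduces. If the SD of 0.35 refers to RDI as defined, it already contains the starting-dose spread, and the unadjusted comparison has the promised power.
- **That the programme cannot affect dosing at all.** This fits only the initial prescription. The ONCORAL programme section has the pharmacist contact the prescriber about interactions, so doses may be revised soon after allocation.

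Other limits also stand. The denominator may already be specific to the patient: if the label gives a dose for reduced renal function or for a combination, a label-based reduction would not lower the ratio. Not every patient needs Table 1 risk factors, because the oncologist's judgement alone can qualify. The planned description of dosage changes will show part of what happens after the start. Finally, RDI is secondary to the incremental cost-effectiveness ratio.

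**Conclusion.** The point holds as a matter of precision and interpretation. RDI includes a component that is, by implication, fixed before randomisation, and the stated analysis makes no use of it.

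The size of the gain cannot be settled from the article. Over assumed r of 0.2 to 0.7 it runs from slight (power about 82%, half-width 0.103) to substantial (about 98%, 0.075). At r near zero the cost is one degree of freedom out of about 190. A non-trivial r is plausible because the starting dose is part of the outcome. It would weigh more in patients with short follow-up, and patients are withdrawn when the agent is changed or stopped, with their data still analysed.

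The conclusion rests on the first dose being prescribed before allocation, on its counting in RDI, and on starting ratios varying between patients. It is an optional improvement, not a fault that threatens the trial's conclusions.

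**What to change.** In the statistical analysis plan, before the database is frozen:

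1. Define the starting-dose ratio as the dose prescribed before randomisation divided by the label dose, with the same denominator as RDI. Say whether that denominator is a single standard dose or the label dose for the patient's situation.
2. Prespecify a linear model for RDI with arm and the starting-dose ratio, using robust standard errors. Report the adjusted mean difference with its 95% CI.
3. Keep the raw description of RDI by arm beside it, together with the planned description of dosage changes.

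The cost is one covariate and a few lines of text, with no added patient or visit. The value should already be on file, since RDI is computed from prescribed doses. If the analysis plan already contains this covariate, nothing needs to change.

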#### Data collection

The course of the study and the details regarding measurement times for relevant data/questionnaires are presented in online supplemental table. Patients will be managed according to standard practice for the follow-up of their cancer: seven visits will be considered for data collection over the 12-month study period, corresponding to the usual consultations with the oncologist or haematologist at the hospital. At each visit, data will be collected from the hospital clinical records, from a dedicated individual booklet filled in by the patient over time, and from the questionnaires. They will be recorded in an electronic case report form. Onsite data monitoring will be planned, and additional data quality control will be performed throughout the study.

The EQ-5D-3L will be self-administered at baseline and at each follow-up visit. This validated instrument contains five dimensions: mobility, self-care, usual activities, pain/discomfort, and anxiety/depression. Each dimension has three levels: no problems, some problems, and extreme problems.

The following resource use will be collected for costs estimation: medical consultations and laboratory and imaging examinations, performed on an outpatient basis and during hospital stay/consultations; nursing care at home; time off work; drugs taken on an outpatient basis; emergency room admissions; and hospital admissions related to OAA complications. The hospital information system of the participating centre will be used to complete hospitalisation data, as well as the French National Health Service data warehouse (ERASME) for ambulatory data.

A specific microcosting study will be carried out to estimate costs related to the implementation of the ONCORAL programme. Hence, the real time spent by the additional hospital staff required for the intervention will be counted, according to the professional category (ie, pharmacist and nurse). This will be self-reported and will relate to the preparation, realisation, and synthesis for each session; the number of actions carried out towards the community health professionals; and the different additional contacts that could take place with the patient.

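### Adverse drug events, interactions and medication errors are defined as raw numbers by arm, although one arm's intervention also detects them and no exposure denominator is given

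*Protocol article*

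**What the plan says.** All references are to the protocol article.

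- **Outcome definitions (Secondary outcomes).** Three entries under the consequences of OAA management are numbers: "Number and type of adverse drug events related to OAA and their grade (2, 3, or 4"; "Number and type of drug–drug interactions related to OAA"; and "Number and type of proven medication errors, with description of their clinical consequences". None carries a rate or a time denominator, and the grade list stops at 4.
- **Intervention arm (The ONCORAL programme).** "Monthly interviews are carried out with a hospital pharmacist and/or a nurse after each consultation with the oncologist or haematologist", or by telephone when no consultation is due. The sessions cover all prescribed drugs, side effects, interactions and self-medication. "If the pharmacist detects an interaction, the prescribing physician is contacted to manage it jointly".
- **Control arm (Usual care).** "There is no intervention from the hospital pharmacist, as OAA is provided by the community pharmacist every month". Consultations are monthly for three months, then three-monthly if treatment is well tolerated.
- **Data capture (Data collection).** Seven visits over 12 months, written for all patients. "At each visit, data will be collected from the hospital clinical records, from a dedicated individual booklet filled in by the patient over time". Questionnaires are a further source.
- **Follow-up and blinding (Study design and settings).** "in the event of a change in treatment and/or complete discontinuation of OAA, the patient will be withdrawn from the study", with the data still analysed. Nobody is blinded.
- **Analysis (Main analyses).** Secondary outcomes are summarised by group without imputation. A log-rank test is named for survival, and mixed models for patient-reported outcomes and quality of life. Nothing further is named for these counts.

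**The concern.** The programme exists to find and resolve drug-related problems. When the number of such problems is also an outcome, a higher count in the ONCORAL arm has two opposite readings: more harm occurred, or more of the same harm was noticed. The definition cannot separate them. The difficulty is sharpest for interactions, because a hospital pharmacist's review of the full drug list takes place in one arm only. It is weaker for severe adverse events, which would usually surface in either arm.

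A second, smaller issue is exposure. Patients leave at OAA change or stop, and the Discussion expects the programme to sustain adherence and raise relative dose intensity. If that also lengthens time on study, the ONCORAL arm has longer to accumulate events.

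A third, separable point is that a fatal OAA-related event (grade 5) falls outside the adverse event count.

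At stake is the interpretation of the safety outcomes closest to the programme's purpose. Counts set side by side in a randomised trial will be read as effects even if no test is attached.

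**Working it through.** **Plan's own figure.** The document gives no event rate, detection probability or on-study time, so there is no figure for these counts to reproduce. The only computed design figure is the sample size for relative dose intensity. With difference 0.15, SD 0.35, 2:1 allocation, two-sided 0.05 and 80% power, the control arm needs 1.5 × (1.960 + 0.842)² × (0.35/0.15)² = 64.1, hence 65, with 130 in ONCORAL. This agrees with the article, and the present point does not touch it.

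**Model.** For counts per patient randomised:

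observed ratio = true rate ratio × (detection ONCORAL / detection control) × (mean time ONCORAL / mean time control).

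Totals per arm would also carry the allocation factor, 143/72 = 1.99, so a per-patient denominator is assumed throughout.

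**Step 1: contact schedules (from the document).** Usual care, if well tolerated: months 1, 2, 3, 6, 9, 12, which is 6 contacts. ONCORAL: monthly, about 12. Ratio 12/6 = 2.

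**Step 2: what contact frequency alone could do.** Assumptions: onset is uniform over 12 months, and an event is noted only if still present at a contact. An event lasting L months is detected with probability equal to the sum over intervals of min(L, gap), divided by 12.

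| L (months) | Usual care | ONCORAL | Ratio |
|---|---|---|---|
| 0.5 | 6 × 0.5 / 12 = 0.25 | 12 × 0.5 / 12 = 0.50 | 2.0 |
| 1 | 6 × 1 / 12 = 0.50 | 12 × 1 / 12 = 1.00 | 2.0 |
| 2 | (3 × 1 + 3 × 2) / 12 = 0.75 | 1.00 | 1.33 |
| 3 | (3 × 1 + 3 × 3) / 12 = 1.00 | 1.00 | 1.0 |

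This is an upper picture: it lets every ONCORAL interview feed the count and ignores the booklet, which can pick up short events in both arms.

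**Step 3: effect on a real benefit.** Control detection is assumed to be 50%.

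| True rate ratio | ONCORAL 60% | 70% | 80% |
|---|---|---|---|
| 0.80 | 0.96 | 1.12 | 1.28 |
| 0.70 | 0.84 | 0.98 | 1.12 |

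A benefit is fully hidden when the detection ratio reaches 1/0.80 = 1.25 or 1/0.70 = 1.43 respectively. Below that it is only diluted.

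**Step 4: on-study time.** With a constant monthly exit hazard h, mean time over 12 months is (1 − exp(−12h))/h. Assumed hazards are OAA stop plus 1% death per month.

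- Stop 4% against 5%: h = 0.05 gives 9.02 months and h = 0.06 gives 8.55; ratio 1.055.
- Stop 6% against 8%: h = 0.07 gives 8.12 months and h = 0.09 gives 7.34; ratio 1.11.
- If the programme instead brought changes forward, swapping the hazards gives 8.55/9.02 = 0.95 and 7.34/8.12 = 0.90.

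Raw counts would move by these factors at equal event rates if events are collected only while on study, which the article does not state. The direction of this component is open.

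**The case against.** Five points on the other side have force.

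1. **No formal comparison is planned.** A reader might infer that the arms are to be tested on these counts. Main analyses only summarises them by group, so the point is about how the displayed figures will be read, not about a flawed test.
2. **Capture is largely shared.** The seven visits are tied to the ordinary consultations and apply to all patients, and the Discussion confirms that control patients complete the booklet and questionnaires. It is tempting to say that the interviews feed the hospital records. No section says so; it is a possible route, since the pharmacist contacts the prescriber about interactions. The mitigation is real but incomplete.
3. **Arm-dependent follow-up is an inference.** The withdrawal rule is identical in both arms. Longer treatment under ONCORAL is plausible from the Discussion but not stated, and earlier recognition of toxicity could act the other way.
4. **Rates and models usually belong in the SAP.** This is correct for the offset alone. The outcome definitions and data sources, however, are set in the article, and that is where the detection problem sits.
5. **Deaths are not lost.** They enter overall survival and the QALYs. Only the adverse event count omits them.

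These points reduce the concern. They do not remove it, because nothing in the article makes identification of interactions or errors independent of arm.

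**Conclusion.** The point holds as a modest one. These outcomes are raw numbers shown by arm in an open trial where one arm's intervention is itself a search for the events. ONCORAL counts are likely inflated by detection, most clearly for interactions and medication errors, and may be shifted further if on-study time differs.

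It would go too far to conclude that the outcomes are biased against ONCORAL by a known amount, or that more detection must look like more harm. Every detection probability and exit hazard above is an assumption. Under those assumptions the detection factor runs from 1.0 to 2.0 and the time factor from 0.90 to 1.11, so a true 20% to 30% reduction may be diluted, hidden or reversed. Size and net direction cannot be computed from the document.

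The outcomes are secondary. They do not enter the ICER or the sample size, so this is a cheap improvement rather than a threat to the main result.

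**What to change.** Specify before database freeze:

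1. **Common sources.** Base the by-arm figures for adverse drug events and medication errors on what is captured at the shared visits and in the booklet. Report items found only at ONCORAL interviews separately, as process measures of the programme.
2. **One interaction check.** Identify interactions in both arms with a single tool, run without the arm label on the drug lists already collected: claims plus drugs recorded by the patient. Claims alone would miss self-medication, which the programme explicitly covers.
3. **Rates beside counts.** Report events per patient-month on study, for example from a Poisson or negative binomial model with a log follow-up offset, and state whether events after withdrawal are counted.
4. **Grade 5.** Include fatal OAA-related events in the adverse event count.

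The cost is SAP wording, analyst time and one run of the interaction tool, with no new patient contact. If the source of each event was not recorded, it will have to be recovered for patients already enrolled (191 when the article was written). The drawback is that some true events seen only at interviews leave the main by-arm figures. Residual bias also remains, because the programme teaches patients to recognise side effects and may change what they write in the booklet.

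### The adverse drug event outcome lists grades 2, 3 or 4 only, so a fatal OAA-related event has no category and no other outcome identifies it

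*Protocol article*

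**What the plan says.** The protocol article's Secondary outcomes section defines the toxicity outcome as "Number and type of adverse drug events related to OAA and their grade (2, 3, or 4"), the grading being "according to the Common Terminology Criteria for Adverse events (CTCAE V.5.0"). The same section lists "Overall survival and progression-free survival" as clinical outcomes and, separately, "Number and type of proven medication errors, with description of their clinical consequences".

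Under Primary outcome, deaths enter the effectiveness measure: "The number of QALYs will be assessed using survival time" together with the EQ-5D-3L.

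Under Main analyses, the general rule is "Data regarding secondary outcomes will be described for each group". For survival, "A Kaplan-Meier model will be used to estimate the overall and the progression-free survival rates", and "a log-rank test will be implemented to compare them". No test is specified for adverse drug events.

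**The concern.** The programme exists to reduce iatrogenic harm from OAAs, and this outcome is the trial's direct measure of drug toxicity. Its grade list is stated explicitly, so this is not a detail that the article leaves to a fuller document. Applied as written, it provides for moderate to life-threatening events but not for the event that kills the patient.

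The direction of any effect on severe toxicity should not be taken for granted. The sample size section expects the programme to raise relative dose intensity from 0.70 to 0.85. An intervention that keeps patients closer to full dose could lower or raise severe toxicity, so the harm comparison should include its most severe end.

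**Working it through.** **The plan's own figures.** The article gives no figure for adverse drug events. Its one reproducible calculation is the sample size for relative dose intensity, which supplies the arm sizes used below. With difference 0.15, SD 0.35, two-sided alpha 0.05, power 80% and a 2:1 ratio:

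- usual care n = (1 + 1/2) × (1.960 + 0.842)² × 0.35² / 0.15² = 1.5 × 7.85 × 5.44 ≈ 64.1, rounded up to 65;
- ONCORAL n = 2 × 65 = 130, and the power at 65 and 130 is 0.805.

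This agrees with the article, which then plans to randomise 143 + 72 = 215. (The abstract says 216; the difference does not matter here.) The point itself does not depend on this calculation.

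**Where an OAA-related death could appear.** Each place in the article that might capture one:

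| Place in the article | Counts the death? | Attributes it to the OAA? |
|---|---|---|
| Adverse drug events, grades 2, 3 or 4 | No category for it | – |
| Overall survival | Yes, any cause | No |
| QALYs (survival time) | Yes, any cause | No |
| Proven medication errors, clinical consequences | Only if a proven error occurred | Only for that error |
| Hospital admissions for OAA complications (Data collection) | Only as resource use for costing | Not as a harm outcome |

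No row both counts and attributes a fatal OAA-related event that occurs without a medication error.

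**Number of events affected (assumed rates).** At 1%, 215 × 0.01 = 2.2; at 3%, 215 × 0.03 = 6.5. That is about 2 to 6 deaths over both arms.

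**Possible distortion between arms (assumed rates).** Suppose 20% of patients in each arm have a serious OAA-related event, some of them fatal, and that fatal events are not counted. The proportion counted is 0.20 minus the fatal proportion.

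| Fatal, ONCORAL / usual care | Counted, ONCORAL (of 143) | Counted, usual care (of 72) | Fatal events uncounted | Apparent difference |
|---|---|---|---|---|
| 1% / 1% | 19% (27.2) | 19% (13.7) | 1.4 / 0.7 | 0 points |
| 3% / 1% | 17% (24.3) | 19% (13.7) | 4.3 / 0.7 | −2 points |
| 5% / 1% | 15% (21.5) | 19% (13.7) | 7.2 / 0.7 | −4 points |

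Total serious toxicity is equal in every row. The apparent difference equals the usual care fatal rate minus the ONCORAL fatal rate, so it is zero when the rates are equal and would run against ONCORAL if usual care had more fatal toxicity.

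**The case against.** **The bracket may not restrict the count.** It qualifies the word grade and might only say which grades are tabulated. A toxicity recorded at grade 2 to 4 at one visit and fatal later might still be counted at its earlier grade. This stands in part: a reader might infer that every fatal event vanishes from the outcome, and the article does not show that. It does show that the fatal result has no category. An event counted at an earlier grade would still not appear as a death.

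**Deaths are not lost to the trial.** A reader might infer that an arm with more fatal toxicity could look safer overall. The article does not support this: those deaths would count against that arm in overall survival, which has a log-rank test, and in the QALYs of the primary outcome. The misleading picture is limited to one descriptive outcome. What survival cannot do, in a cancer population, is show which deaths were due to the drug.

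**The size and direction are assumed.** This stands. The article gives no fatal-toxicity rate and nothing to suggest that the rates differ by arm; 5% against 1% is an illustration only.

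**The meaning of grade 5 is not in the article.** It names CTCAE version 5.0 without describing the grades. That grade 5 denotes death is the scale's standard convention and is used here as an assumption.

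**The article condenses a fuller protocol.** Safety reporting may be set out there. That would not change the grade list stated here for the outcome.

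**Conclusion.** The point holds as a minor defect in the definition of one secondary, descriptive outcome. The listed grades give a fatal OAA-related event no category, and no other outcome distinguishes OAA-related deaths from other deaths.

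Two consequences differ in certainty. The omission of the fatal category follows from the wording if the list is read as it stands, and it applies even when fatal rates are equal. The distortion between arms is conditional: it needs unequal fatal rates and fatal events not already counted at a lower grade. The 2 to 6 deaths and the 0 to 4 points rest entirely on assumed rates. The primary analysis, the survival analyses and the sample size are unaffected.

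**What to change.** Define the outcome as OAA-related adverse drug events of grade 2 or higher, including grade 5. Report OAA-related deaths per arm as a separate line beside all-cause deaths.

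No new visits or patients are needed: deaths are already required for overall survival, and hospital records are already a data source. The cost lies in attribution. The article reports 191 patients already randomised, so the cause of some deaths must be judged in retrospect. Allocation is open to medical and trial staff, and there is no independent monitoring committee, so knowledge of the arm could colour the judgement. The attribution criteria should therefore be fixed before the database freeze and, where feasible, applied from records that do not show the arm.

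The change does not cure a related problem: a patient who dies contributes no later grade 2 to 4 events, whatever the cause of death. The event counts should be read with that in mind.
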